### Statistical analysis

#### *Sample size*

Progression free survival of patients in the control arm is estimated at ten months. An increase in progression free survival of at least five months in favor of the experimental treatment is considered acceptable given the expected surgery related morbidity. To detect a constant hazard ratio of 1.5 with a 0.05 two-sided significance level and a power of 80%, 104 patients should be enrolled in each arm. Assuming an accrual period of five years, three years of follow-up and 10% loss to follow up, 230 patients need to be included.

### Interim analysis

An interim analysis for efficacy is planned at two months after randomisation of the last patient. Whatever the outcome of the interim analysis, all randomised patients will be followed until 36 months after randomisation of the last patient. This means that even in case of a statistically significant treatment effect, the trial will not be stopped. The objective of this interim analysis is that patients who are not participating in this study might profit in case of early positive results. The Peto-Haybittle rule, that requires P <0.001 as evidence, will be applied. This leaves the significance level of the final primary efficacy analysis at 0.0498.

### Data analysis

The results of the study will be analyzed according to the intention to treat principle. All patients will be included in the analysis and patients lost to follow-up will be regarded as censored observations. Progression free and overall survival in both treatment arms will be calculated by the Kaplan-Meier method and compared by using the log-rank test, assuming that the hazard rates in the two treatment arms are roughly proportional over time. If mortality due to surgery is unexpectedly high, resulting in proportional hazard (PH) assumptions that are not valid, the primary comparison of the treatment groups will be based on the one-year progression-free disease rates. In addition, progression free and overall survival since start therapy and after the sixth chemotherapy cycle will be compared.

To adjust for baseline covariates, we will also estimate the treatment effect by Cox’s proportional hazard (PH) regression model, given that the PH assumptions are valid. If the mortality due to surgery is unexpectedly high, resulting in PH assumptions that are not valid, progression free survival since start chemotherapy will be analyzed. At least the following baseline covariates will be considered: completeness of primary surgery, FIGO stage, ECOG performance status, age, disease free interval and CA-125 at recurrence. The significance level of the final primary analysis will be set at 0.0498, and for the interim analysis at 0.001. For all other analyses, 0.05 will be used in the report of study results.

Treatment related morbidity at 30 days after surgery will be analysed with descriptive statistics. Logistic regression will be used to study relations between clinical variables and morbidity. Toxicity after the third and sixth chemotherapy course will be evaluated by means of descriptive statistics and by using an unpaired Student’s t-test or the two-sided Mann-Whitney test for the continuous variables. Comparisons of the proportions of toxicity between the 2 arms will be done by use of a two-sided chi-square test or a two-sided Fisher’s exact test if the number of expected patients in a given category is less than five.

Quality of life scores will be summarized per time-point, for those subjects, who are alive, once for the original values and once for the changes from baseline. Only subjects who have filled in a baseline questionnaire will be included in the analysis. In addition to descriptive statistics, the Quality Adjusted Life Years (QALY) will be analysed. QALYs will be based on the EQ-5D-3 L questionnaire. The repeated measures indexes will be combined over time using the trapezium rule (area under the Quality Adjusted Life Year curve).

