### Randomisation

Randomisation is performed by accessing a central internet-based randomisation programme. Stratification will be done for gynaecologic-oncologic center hospital and completeness of primary cytoreductive surgery (complete vs optimal). Patients will be randomly allocated to both arms in a 1:1 ratio. To ensure patients privacy, patients will be registered by study trial number after randomisation.

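### The primary log-rank test names no strata although randomisation is stratified by completeness of primary surgery; the test stays valid but loses power if that factor affects progression-free survival

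*Protocol article*

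**What the plan says.** Under Randomisation, the protocol article states: "Stratification will be done for gynaecologic-oncologic center hospital and completeness of primary cytoreductive surgery (complete vs optimal"). It adds: "Patients will be randomly allocated to both arms in a 1:1 ratio".

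Under Data analysis, progression-free and overall survival "will be calculated by the Kaplan-Meier method and compared by using the log-rank test". No strata are named. Adjustment is placed in a second, separate analysis: "To adjust for baseline covariates, we will also estimate the treatment effect by Cox’s proportional hazard (PH) regression model". The covariates to be considered, given as a minimum list, are "completeness of primary surgery, FIGO stage, ECOG performance status, age, disease free interval and CA-125 at recurrence". Completeness of primary surgery is on that list; centre is not.

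The same section sets the level of the final primary analysis at 0.0498. The Sample size section gives 104 patients per arm and 230 in total, with no term for a prognostic factor.

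**The concern.** Stratified allocation makes the arms nearly equal within the complete and optimal groups. If these groups differ in PFS, the numerator of the log-rank statistic varies less from trial to trial than it would under simple randomisation. The unstratified variance formula does not take account of this, so the statistic is too small on average and the P-value too large. Pooling groups with different hazards also pulls the marginal hazard ratio towards 1. Both effects reduce power.

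What is at stake is efficiency on the primary endpoint. The design aims at 80% power with little to spare, so a loss of a few points takes the trial below its own target. The information that would prevent this is already collected for randomisation.

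**Working it through.** **Inputs from the protocol.** Control PFS: "Progression free survival of patients in the control arm is estimated at ten months". Effect: "To detect a constant hazard ratio of 1.5 with a 0.05 two-sided significance level and a power of 80" per cent. Accrual is 5 years, further follow-up 3 years, loss 10%, total 230, and the final level 0.0498.

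**Step 1: the stated sample size.**
- Freedman: events = (1.960 + 0.842)² × [(1.5 + 1)/(1.5 − 1)]² = 7.849 × 25 = 196.2, so 197.
- Event probability with exponential PFS and uniform accrual: 1 − [exp(−36λ) − exp(−96λ)]/(60λ). With λ = ln 2/10 this is 0.980; with λ = ln 2/15 it is 0.936; the mean is 0.958.
- Patients: 197/0.958 = 206, or 103 per arm (stated: 104).
- Loss: 208/0.9 = 232, or 208 × 1.1 = 229 (stated: 230).

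The figure reproduces. The calculation contains nothing for a prognostic factor. 208 patients give 208 × 0.958 = 199 events against the 197 needed, so the margin is small.

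**Step 2: the two tests.** With g the arm indicator and p the proportion at risk in the experimental arm at each event, U = Σ(g − p) and V = Σp(1 − p).
- Unstratified: Z = U/√V over all patients.
- Stratified by completeness: Z = (U₁ + U₂)/√(V₁ + V₂), computed within the complete and optimal groups and then summed.

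**Step 3: simulation.** 230 patients, 9 centres, exponential PFS, 36–96 months of follow-up, about 8–10% loss, two-sided level 0.0498, and a treatment hazard ratio of 1.5 within strata. Assumptions not in the protocol: permuted blocks of four within centre by completeness, the prognostic hazard ratio, and the share with optimal surgery. There were 10,000 runs per scenario; the standard error is about 0.4 points for power and 0.2 for type I error.

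| Prognostic HR | Share optimal | Power, unstratified | Power, stratified | Loss (points) | Type I, unstratified | Type I, stratified |
|---|---|---|---|---|---|---|
| 1 | 30% | 81.0% | 80.4% | −0.5 | 5.1% | 5.0% |
| 1 | 50% | 81.9% | 81.5% | −0.4 | 4.9% | 5.0% |
| 1.25 | 30% | 81.0% | 81.4% | 0.4 | 5.0% | 5.0% |
| 1.25 | 50% | 81.0% | 81.0% | 0.1 | 5.3% | 5.4% |
| 1.5 | 30% | 79.7% | 80.9% | 1.2 | 4.4% | 4.7% |
| 1.5 | 50% | 79.1% | 80.7% | 1.6 | 4.8% | 5.2% |
| 2 | 30% | 76.5% | 80.6% | 4.1 | 4.4% | 5.0% |
| 2 | 50% | 74.8% | 80.5% | 5.7 | 4.0% | 5.0% |
| 3 | 30% | 71.6% | 80.3% | 8.7 | 3.8% | 5.3% |
| 3 | 50% | 66.3% | 79.7% | 13.4 | 3.4% | 5.5% |

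Losses are computed before rounding. The highest stratified type I error, 5.49%, is (5.49 − 4.98)/0.22 = 2.3 standard errors above nominal, one of ten null scenarios.

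**Step 4: check on the mechanism.** At a prognostic hazard ratio of 2 with 50% optimal, the null standard deviation of the unstratified Z is 0.956. The critical value for 0.0498 is 1.962, so the expected type I error is 2[1 − Φ(1.962/0.956)] = 2[1 − Φ(2.052)] = 0.040, which matches the simulated 4.0%.

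**Step 5: smaller optimal group.** With 20% optimal (6,000 runs), power was 80.1% against 80.7% at a prognostic hazard ratio of 1.5 (loss 0.6 points) and 78.7% against 80.6% at 2 (loss 1.9). At 2.5, with 20–40% optimal (4,000 runs), the loss was about 4–8 points.

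**Step 6: using all randomisation strata.** Stratifying the test by the 9 × 2 = 18 cells gave power of about 72–76% (5,000 runs per scenario, no centre effect assumed), because the cells are sparse.

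**The case against.** The strongest reply is that the article never says the test is unstratified. It condenses a fuller protocol, an analysis plan may exist, and strata are often named there. This stands in part: strata may already be specified elsewhere. But the section does fix the primary test, its level and a fallback, and it puts adjustment in a separate model that is estimated in addition. The plain reading is a test without strata.

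The second reply is that the loss depends on figures the protocol does not give. This stands. A reader might infer from the Background that completeness of primary surgery is prognostic for PFS. The text does not support that: it names the factor as a predictor of achieving complete resection at secondary surgery, which control patients do not undergo. Eligibility also narrows the contrast to no residual disease against at most 1 cm.

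The third reply is that the planned Cox model already includes completeness. This stands for the adjusted hazard ratio, but that model is supportive and does not restore the power of the primary test. A reader might also count the absence of centre from the covariate list as an error. The list is a minimum and does not exclude centre, and how to handle centre is a matter of preference.

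**Conclusion.** The point holds as an efficiency improvement, conditional on the factor being prognostic. With 20–50% optimal, the loss is about 0–2 points at a prognostic hazard ratio of 1.5 or less and about 2–6 points at 2. At 3 it reaches about 9–13 points with 30–50% optimal. The prevalence and the prognostic hazard ratio are both assumed.

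A reader might go further and infer that the primary test is invalid, or that the Randomisation and Data analysis sections contradict each other. Neither follows. Any departure from the nominal level is conservative: unstratified type I error is about 4.0–4.4% at a prognostic hazard ratio of 2. Nothing favours surgery spuriously. Nor is there a rule that test strata must match every randomisation stratum; matching all 18 cells here would cost more power than it gains.

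**What to change.** State that the primary PFS comparison is a log-rank test stratified by completeness of primary surgery (complete or optimal) only, with the hazard ratio from a Cox model stratified the same way. Report the unstratified log-rank test as a sensitivity analysis. Do not stratify the test by the 18 centre-by-completeness cells. The covariate-adjusted Cox model can stay as planned.

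The cost is one sentence in the protocol or analysis plan, with no extra patients or data, and about half a point of power if the factor turns out to have no effect. The change should be fixed before the interim efficacy analysis. If the full protocol or analysis plan already names these strata, confirming that is enough.

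### The plan moves the primary test from log-rank to one-year progression-free rates on a condition judged from outcomes by arm, and the trial is not sized for that second test

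*Protocol article*

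**What the plan says.** The Data analysis section compares PFS between the arms by log-rank, on the premise of roughly proportional hazards. It then adds a conditional rule. If deaths from surgery are more frequent than expected and proportionality fails as a result, "the primary comparison of the treatment groups will be based on the one-year progression-free disease rates". Under the same condition, the covariate-adjusted analysis moves to PFS counted from the start of chemotherapy. On the level of the test: "The significance level of the final primary analysis will be set at 0.0498, and for the interim analysis at 0.001".

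The Sample size section gives one calculation. On the control arm it says "Progression free survival of patients in the control arm is estimated at ten months". The target is worded as "An increase in progression free survival of at least five months in favor of the experimental treatment is considered acceptable". The calculation is set up with the words "To detect a constant hazard ratio of 1.5 with a 0.05 two-sided significance level and a power of 80" per cent, and its result is a figure of 104 for either arm. The total is then reached as follows: "Assuming an accrual period of five years, three years of follow-up and 10% loss to follow up, 230 patients need to be included". The section states no power for a one-year comparison and no expected surgical mortality; it mentions only expected morbidity.

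**The concern.** Both parts of the condition, excess surgical deaths and failed proportionality, can be judged only from outcomes by arm. The rule therefore lets the data to be tested decide which primary test is used.

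The reason given does not require a change of test. At each event time, the log-rank test compares the observed events in an arm with those expected from the numbers at risk. If the two PFS curves are equal, that comparison is valid whether or not proportional hazards would hold otherwise. Non-proportionality affects the power of the test and the meaning of a single hazard ratio.

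The replacement ignores every difference after month 12. Early surgical deaths lower the experimental curve at month 12, and any later benefit that might offset them is discarded. At stake are the power of the primary analysis when the rule is invoked and, to a smaller degree, the 0.0498 level.

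**Working it through.** **Inputs from the Sample size section.** Control PFS of 10 months and experimental PFS of 15 months, read as exponential medians (an assumption, consistent with the constant hazard ratio: 15/10 = 1.5). Accrual 60 months, taken as uniform; further follow-up 36 months; 104 per arm, or 115 per arm (230/2). The Randomisation section gives the ratio: "Patients will be randomly allocated to both arms in a 1:1 ratio". Two-sided level 0.0498, so the critical value is 1.962.

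**The plan's own figure.**
- Probability of an event by the final analysis = 1 − exp(−36λ) × [1 − exp(−60λ)]/(60λ), with λ = ln 2/median. This gives 0.980 (control) and 0.936 (experimental), mean 0.958.
- Freedman: (2.5/0.5)² × (1.960 + 0.842)² gives 197 events. Dividing by 2 × 0.958 gives 103 per arm, against 104 stated. Schoenfeld: 191 events, 100 per arm.
- Loss: 208 × 1.10 = 229 and 208/0.90 = 232 (rounded up to an even total), against 230 stated. The sample size is reproduced.

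**Log-rank power on the design assumptions.** Events = 208 × 0.958 = 199. √(199.3/4) × ln 1.5 = 2.862; 2.862 − 1.962 = 0.900; power 81.6%. With 115 per arm and no loss: 220 events, 85.3%.

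**One-year comparison on the same assumptions.**
- One-year PFS = exp(−12 ln 2/median): 43.5% and 57.4%, a difference of 13.9 points.
- 104 per arm: SE = √[(0.435 × 0.565 + 0.574 × 0.426)/104] = 0.0687; z = 0.1391/0.0687 = 2.03; power 52.5% (51.8% pooled, 51.4% complementary log-log).
- 115 per arm: 56.7% (55.9% pooled, 55.5% complementary log-log).
- About 202 per arm would be needed for 80%.

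**With early surgical deaths (assumed rates).** A fraction m of the experimental arm dies within the first 1.5 months; the rest follow the design. For the one-year rates, experimental PFS is (1 − m) × 57.4%:
- m = 5%: 54.6%, difference 11.0 points, SE 0.0689, power about 36%.
- m = 10%: 51.7%, difference 8.2 points, SE 0.0690, power about 22%.

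Simulation, 4,000 runs per row, log-rank against the 12-month Kaplan-Meier difference:

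| Early deaths | Per arm | Log-rank | One-year |
|---|---|---|---|
| none | 104 | 80.7% | 53.8% |
| none | 115 | 85.5% | 58.8% |
| 5% | 104 | 68.0% | 36.3% |
| 10% | 104 | 49.7% | 23.6% |

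A second simulation at 104 per arm gave 81% v 51%, 68% v 35% and 49% v 21%, and 85% v 58% at 115 per arm without early deaths. Across the scenarios with early deaths, the one-year test loses about 26 to 33 points.

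**Type I error.** With identical curves, at least one of the two tests was significant in 9.2% of runs (104 per arm) and 8.3% (115 per arm), with a simulation error of about half a point. Log-rank alone gave 6.0% and 5.0%. The 8-9% is what a completely free choice between the tests would produce.

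**The case against.** The other side has good points, and several limit what can be said.

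- A reader might infer that the plan cuts its power from 80% to 52%. The documents do not support that. The 52% assumes proportional hazards, and the switch applies only when they fail. With a 5%-level proportional-hazards test as a stand-in for the trigger (an assumption), the whole procedure kept about 80% power under the design alternative, against 82% for log-rank alone. Where the trigger is met, log-rank is itself below 80% in the scenarios tested.
- A reader might take 8-9% as the plan's type I error. It is an upper bound. The rule runs one way only and is tied to excess surgical deaths. With the same stand-in trigger the null rate was 5.5-5.9%, against 5.3% for log-rank alone. In the scenarios with early deaths, the switch also leads to the test less likely to favour surgery, so it is a poor route to a positive result.
- A reader might fault the article for giving no mortality threshold or proportional-hazards criterion. Such detail may stand in a full protocol or SAP that is not shown, and its absence alone is no finding. The data safety monitoring board also reviews deaths every six months against the literature, which is an independent though unquantified reference.
- A one-year milestone named in advance is a recognisable choice. With early deaths and later benefit, an average hazard ratio is hard to read.

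The last point stands as a reason to report 12-month PFS. It is not a reason to make it the primary test. The conditional change of test is itself written in the article, so the concern does not depend on missing detail.

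**Conclusion.** The point holds in a limited form and is a should-fix. The stated rule makes the primary test depend on outcomes by arm, for a reason that does not make log-rank invalid, and moves to a comparison the trial is not sized for. At equal sample size, the one-year test was roughly 26 to 33 points less powerful than log-rank in every scenario examined.

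The figures rest on exponential PFS with medians of 10 and 15 months. The trigger scenarios also rest on assumed surgical death rates of 5% and 10% and a hazard ratio of 1.5 persisting afterwards, none of which the article gives for that case. The effect on type I error is likely to be modest and cannot be fixed exactly without an operational trigger. The sample size calculation is not in error.

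**What to change.** Delete the switch. State that log-rank on PFS from randomisation is the primary test at 0.0498 whatever the check of proportional hazards shows. Pre-specify, as supportive estimates, the Kaplan-Meier PFS at 12 months by arm and the difference in restricted mean PFS to a fixed horizon; 36 months lies within every patient's planned follow-up. Give these prominence in the interpretation if the curves cross. The parallel clause for the covariate-adjusted analysis uses the same trigger and should be brought into line.

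The cost is wording only, with no added patients. The small downside is that under crossing hazards the hazard ratio is an average over follow-up and must be read with the supportive estimates.

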#### *Primary outcome measure*

Primary outcome measure is progression free survival, defined as the interval between the date of randomisation and the date of progressive disease or death of any cause, whatever occurs first. Progressive disease defined as clinical and radiological signs of recurrence (RECIST 1.1 criteria) [12] or elevated CA 125 (GCIG criteria) and radiological signs of recurrence (RECIST 1.1 criteria) [13].

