#### *Secondary outcome measures*

Secondary outcome measures are overall survival, progression free survival since start therapy and after the sixth chemotherapy cycle, quality of life during two years after treatment (EORTC QLQ-C30 version 3.0 and QLQ-OV28, EQ-5D), surgery related morbidity and mortality, toxicity (NCI-CTC Toxicity Scale Version 4.0), tumor response following treatment (RECIST and GCIG criteria).

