### Interventions

#### *Control arm*

Patients in the control arm will receive at least six courses of platinum-containing chemotherapy. The first course should be given as soon as possible but within 4 weeks after randomisation. Chemotherapy dose and schedule, combination with other chemotherapeutic agents and pre-and post-chemotherapy medication and hydration is left to the discretion of the participating center. Before every chemotherapy cycle, hematological, renal, and hepatic function will be determined and toxicity is scored using the common toxicity criteria for adverse effects (CTCAE) version 4.0.

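### PFS and OS counted from the sixth chemotherapy cycle are tested between arms at 0.05, although the groups entering that comparison are no longer the randomised groups

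*Protocol article*

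**What the plan says.** All statements are in the protocol article.

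- **Primary outcome measure.** PFS is "defined as the interval between the date of randomisation and the date of progressive disease or death of any cause, whatever occurs first".
- **Data analysis, analysis set.** The analysis is by intention to treat: "All patients will be included in the analysis and patients lost to follow-up will be regarded as censored observations".
- **Data analysis, same paragraph.** "In addition, progression free and overall survival since start therapy and after the sixth chemotherapy cycle will be compared". Nothing labels these comparisons descriptive, exploratory or conditional on reaching the later starting point.
- **Data analysis, significance levels.** "The significance level of the final primary analysis will be set at 0.0498, and for the interim analysis at 0.001". Then: "For all other analyses, 0.05 will be used in the report of study results".
- **Secondary outcome measures.** The list opens: "Secondary outcome measures are overall survival, progression free survival since start therapy and after the sixth chemotherapy cycle". Only PFS is listed with the later time origins. OS from those origins appears only under Data analysis.
- **Control arm.** For chemotherapy: "The first course should be given as soon as possible but within 4 weeks after randomisation".
- **Experimental arm.** Surgery is due within 4 weeks of randomisation, and chemotherapy within 6 weeks after surgery.

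**The concern.** A clock that starts after the sixth cycle admits only patients who reached that point. Anyone who died or stopped chemotherapy earlier is out and, for PFS, so is anyone who progressed. What removes patients before then differs by arm (surgery plus chemotherapy against chemotherapy alone), and so does the length of time over which they can be removed. Randomisation balances the arms at entry to the trial. It does not balance those still in contention five to six months later.

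The text nevertheless treats the result as an ordinary arm comparison with a 0.05 threshold, under a sentence saying that all patients are included. Both cannot be true of this comparison. Surgical deaths, which the same section foresees as a possible problem, are invisible to it. At stake is a secondary result that could point the other way from the randomised one without any true later effect of surgery.

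**Working it through.** **1. The plan's own figure.** Under Sample size the control median PFS is 10 months, the gain 5 months, the HR 1.5, two-sided alpha 0.05 and power 80%, with 5 years of accrual and 3 of follow-up. Freedman events: ((1.5+1)/(1.5−1))² × (1.960+0.842)² = 25 × 7.85, giving 197. With exponential medians of 10 and 15 months, uniform accrual over 60 months and 36 months' minimum follow-up, the event probabilities are 0.980 and 0.936, mean 0.958. Then 197/0.958 = 206, or 103 per arm against the stated 104. For 10% loss, 208 × 1.10 = 229 and 208/0.90 = 231, either side of 230. The design therefore fits exponential medians of 10 and 15 months, which are used below.

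**2. When the clock starts.** Windows are from the arm descriptions. Cycle length is left to the centres, so 3 weeks is an assumption.

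- Control: 4 + 6 × 3 = 22 weeks = 22/4.345 = 5.06 months.
- Surgery: 4 + 6 + 6 × 3 = 28 weeks = 28/4.345 = 6.44 months.

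**3. PFS events before the clock starts.** Share = 1 − 0.5^(t/median).

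| Arm | Median (months) | t (months) | Event before start | Left of 115 |
|---|---|---|---|---|
| Control | 10 | 5.06 | 29.6% | 81 |
| Surgery, target effect | 15 | 6.44 | 25.8% | 85 |
| Surgery, no effect | 10 | 6.44 | 36.0% | 74 |

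With 3- or 4-week cycles, and either maximum windows or short ones (1 week to first treatment, 3 from surgery to chemotherapy), the share still event-free is 64–74% in control and 70–79% under surgery (58–70% if surgery has no effect). So roughly 20–40% of randomised patients leave the PFS comparison, before counting those who stop chemotherapy early. The documents give no design assumption for OS, so no OS share is computed.

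**4. Effect on the PFS hazard ratio.** Simulated trials had 115 per arm, control median 10 months and log-rank HRs, surgery over control. Gamma frailty represents prognostic differences between patients.

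*5% surgical deaths, no other effect:*

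| Frailty variance | HR from randomisation | HR after sixth cycle | HR from common week-28 landmark | Excluded, control / surgery |
|---|---|---|---|---|
| 0.5 | 1.05 | 0.97 | 1.00 | 32% / 41% |
| 1.0 | 1.05 | 0.95 | 1.00 | 34% / 42% |

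The after-sixth-cycle test rejects about 6% of the time, and 4–5% in favour of surgery against a nominal 2.5%.

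*No true effect after the clock starts, early hazard under surgery varied, frailty variance 0.5 to 2:*

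| Early hazard, surgery vs control | HR from randomisation | HR after sixth cycle | Rejection after sixth cycle |
|---|---|---|---|
| Equal | 1.00 | 0.97 to 0.93 | 5–7% |
| Doubled | 1.28 to 1.17 | 0.84 to 0.71 | 14–30% |
| Halved | 0.86 to 0.89 | 1.05 to 1.12 | 6–8% |

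With essentially no frailty, the after-sixth-cycle HR is 1.00–1.01 and rejection 5% throughout.

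The equal-hazard results (0.97 at variance 0.5, 0.95 at 1.0) match those with 5% surgical deaths. In that scenario the shift therefore comes from the unequal starting times, and the deaths simply drop out of sight. The bias can run either way: an early benefit of surgery makes the later comparison look unfavourable to it.

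**5. Since start of therapy.** First treatment is due within 4 weeks in both arms, and 4/4.345 = 0.92 months. Event-free shares are 0.5^(0.92/10) = 94% and 0.5^(0.92/15) = 96%. With equal early hazard the HR is 0.99–1.00 and rejection about 5%.

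**The case against.** The case for leaving the text alone has four parts.

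- **The primary result is protected.** It runs from randomisation in all patients, OS is compared in the same way, and the disputed analyses are additions. This stands. A reader might infer that the trial's main conclusion is compromised, but nothing in the article lets these comparisons replace it.
- **The bias is small and rests on assumptions.** Frailty, surgical mortality and cycle length are not in the documents. Without heterogeneity there is no bias, and the larger distortions need a doubled early hazard that the article does not suggest. This stands as to size: a reader should not infer that a spurious significant benefit is likely. It does not remove the defect, because the article itself plans adjustment for six prognostic covariates and so expects patients to differ.
- **An article condenses.** How non-completers are handled may be set out in the full protocol. That is fair for the handling rules. It does not reach the stated choice to compare arms from this origin at 0.05.
- **The two later origins are not alike.** A reader might extend the criticism to the comparison since start of therapy. The documents do not support that. Entry needs only that first treatment begins, surgical deaths fall after that clock starts and are counted, and the article names start of chemotherapy separately for its fallback analysis. Nor does OS after the sixth cycle require being progression-free; it requires being alive with six cycles given.

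**Conclusion.** The point holds for PFS and OS after the sixth cycle. The article plans a between-arm test at 0.05 in groups defined by a post-randomisation state, reached by different routes and up to six weeks later under surgery. Its intention-to-treat statement cannot cover that test. Under the assumed cycle length and windows, about 30% and 26% of patients have a PFS event before the clock starts at the design medians. The modelled distortion is modest: HR 0.95 to 0.97 where the analysis from randomisation gives about 1.05, with 5% surgical deaths and frailty variance 0.5 to 1.0. It grows with a higher early hazard under surgery and vanishes without heterogeneity. The text should be corrected, but the primary analysis is not threatened and the comparison since start of therapy need not be removed.

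**What to change.** - Under Data analysis, base between-arm inference on PFS and OS from randomisation.
- Report PFS and OS after the sixth cycle per arm, labelled descriptive and conditional on reaching that point, without p-values. Give the number not reaching it in each arm, by reason (death, progression, stopping chemotherapy, other).
- Under Secondary outcome measures, mark the after-sixth-cycle PFS entry in the same way.
- If a later-phase contrast is wanted, use one fixed landmark time from randomisation in both arms, labelled exploratory, with exclusions by arm. This removes the timing difference (HR 1.00 in the 5% surgical-death scenario). It still conditions on surviving to the landmark, so it cannot be confirmatory.

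The cost is a few sentences and the loss of the after-sixth-cycle p-values for PFS and OS. Sample size, data collection and the primary analysis do not change.
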